## Abstract

**Background:**

Although it is widely acknowledged that food intake can worsen symptoms in patients with irritable bowel syndrome (IBS), there is a lack of efficient treatments that can apply to all patients and subtypes of IBS. As IBS can manifest in different ways, it is likely that the most successful treatment option will differ among patients; therefore, this large, randomized controlled trial comparing 3 different treatment options for patients with IBS is highly warranted.

**Objective:**

This study aims to conduct a randomized controlled trial to evaluate the effectiveness of 3 different treatment options for patients with IBS.

**Methods:**

A total of 300 patients with IBS will be randomized (1:1:1) to receive one of the following three treatment options: a diet with low total carbohydrate content; a diet combining low fermentable oligosaccharides, disaccharides, monosaccharides, and polyols and traditional dietary advice in IBS; and optimized medical treatment. The study will comprise a 10-day screening period, 28 days of intervention, and a 6-month follow-up for patients receiving dietary treatment. Questionnaires assessing both gastrointestinal and extraintestinal symptoms will be used as end points, as well as metabolomics, microbiota profiling, and immunological markers. Furthermore, qualitative methods will be used to evaluate the patients’ experiences regarding diet treatments.

**Results:**

Recruitment for this study began in January 2017. By May 2021, of the proposed 300 participants, 270 (90%) had been randomized, and 244 (81.3%) participants had finished the 4-week intervention. The study is still in progress, and the results are expected to be published in 2022.

**Conclusions:**

By collecting a wide range of data before, during, and after treatment in a large group of patients with IBS and diverse bowel habits, we will gain new insights into the predictors of response to treatment. That information can, in the future, be used to personalize treatment for the patient, based on the individual’s phenotype and IBS symptoms. In addition, the long-term effects of 2 different dietary treatments will be evaluated regarding their impact on gut microbiota and clinical laboratory tests and to ensure that they are safe, effective, and applicable for patients with IBS.

**Trial Registration:**

ClinicalTrials.gov NCT02970591; https://clinicaltrials.gov/ct2/show/NCT02970591

**International Registered Report Identifier (IRRID):**

DERR1-10.2196/31413

## Introduction

### Background

Irritable bowel syndrome (IBS) is a functional gastrointestinal (GI) disorder characterized by abdominal pain and altered bowel habits [1]. Some of the pathophysiological traits of IBS include disturbed gut–brain interactions, GI motility abnormalities, visceral hypersensitivity, or altered gut microenvironments, including unfavorable gut microbial composition [2-4]. However, available treatment options are limited, which leads to unsatisfactory symptom relief in many patients. This leads to a reduced quality of life (QoL) and impaired working ability, with substantial costs for both the individual and society [5].

Most patients with IBS report that their GI symptoms are diet related [5-7]. Different dietary approaches have been proposed to reduce symptoms of IBS [8]. Traditional dietary advice based on the National Institute for Health and Care Excellence (NICE) guidelines focuses on limiting foods that are recognized to provoke symptoms and emphasizes regular meal intake and portion size control [9]. A diet comprising a low amount of fermentable carbohydrates—the low fermentable oligosaccharide, disaccharide, monosaccharide, and polyol (FODMAP) diet—is currently also used as a treatment option for reducing GI symptoms in patients with IBS, most frequently as a second-line treatment option [10]. FODMAPs are found in a wide range of legumes, certain vegetables and fruits, cereals (wheat, rye, and barley), dairy products, and food items containing sweeteners. The intake of FODMAPs is believed to cause symptoms through bacterial fermentation and increased gas production. This, in combination with increased water retention through osmosis, distends the colon and can cause pain and other IBS-related symptoms in susceptible individuals, for example, those with visceral hypersensitivity [11,12]. This dietary regime has been tested in several randomized trials and seems to be effective in 50%-80% of patients with IBS [13]. To our knowledge, no trial has tested the combined effect of traditional dietary advice together with low FODMAP content.

It has been acknowledged that patients who adhere to a low-carbohydrate, high-fat diet for weight loss purposes, or to lower their blood glucose levels, have reported fewer GI symptoms when following this diet [14]. A pilot study investigated the effects of a diet with low-carbohydrate content in patients with IBS, and although the sample size was small, the effect was very promising [15]. However, most patients seeking help for their IBS complaints will most likely see a primary care physician who frequently offers various prescription drugs. To date, no study has compared the effect of a strategy where pharmacological treatment options are used with a diet low in total carbohydrate content, or a low FODMAP diet is used in combination with traditional dietary advice for patients with IBS.

As IBS is a heterogeneous disease with different predominant symptom patterns and underlying pathophysiological traits, personalized treatment options are needed. A better understanding of the predictors of a favorable outcome with different treatment options can facilitate this and reduce the overall symptom burden in this large patient group, which, in turn, could reduce costs for society and the individual. Therefore, a large, randomized trial comparing the effects of these 3 different treatment strategies for patients with IBS, with a thorough examination of the factors predicting treatment outcomes, is warranted.

### Research Objectives and Hypotheses

The aim of this study is to compare the effectiveness of three different treatment options for patients with IBS: a low-carbohydrate diet (LCD), a diet combining low FODMAP and traditional dietary advice (LFTD), and optimized medical treatment (OMT). The trial has been registered at ClinicalTrials.gov NCT02970591.

#### Specific Aims

The specific aims of this study are as follows:

To compare the response to 3 different treatment options for IBS, defined as a reduction in IBS symptom severity score by ≥50, in a 4-week randomized controlled trial using the validated IBS Severity Scoring System (IBS-SSS) [16]To study the effects of these treatment options on QoL, anxiety and depression, fatigue, extraintestinal symptoms, metabolic factors, gut microbiota, and immunological markersTo study the extent to which participants choose to maintain their allocated diet and whether it will be possible to reintroduce certain amounts of FODMAPs successfully and assess the long-term effects on global IBS symptoms, metabolic factors, and gut microbiota during a 6-month postintervention follow-upTo identify pretreatment factors, such as sociodemographic factors, IBS symptom severity, predominant IBS symptoms, extraintestinal symptoms, psychological factors, microbiota composition, and metabolic fingerprints that can predict response to the treatmentsTo evaluate the participants’ subjective experiences related to dietary treatment using qualitative methods

#### Study Hypotheses

The primary hypothesis is that a diet combining low FODMAP and traditional dietary advice would improve GI symptoms in a larger proportion of patients than LCD or OMT. The secondary hypotheses to be tested are as follows: (1) the reduction in GI symptoms depends on the compliance to the allocated intervention; (2) it is possible to reintroduce FODMAPs in a systematic manner after a 4-week elimination with sustained effect on GI symptoms; (3) the degree to which the patients maintain their allocated diet during the 6-month follow-up depends on how large the symptom reduction was during the intervention period; (4) a treatment aimed at reducing GI symptoms will also favorably affect extraintestinal symptoms, microbiota composition, QoL, work productivity, and psychological factors; and (5) a combination of microbiota composition, metabolic fingerprint, and GI symptom pattern can predict the treatment outcomes.

## Methods

### Study Setting and Design

The study will be conducted in an outpatient clinic specializing in functional GI disorders at the Sahlgrenska University Hospital, Gothenburg, Sweden, beginning in January 2017. This will be a single-center, single-blinded, randomized controlled trial.

### Allocation

Patients will be randomly assigned to receive 1 of the 3 treatments in a ratio of 1:1:1. For the allocation of the patients, an external web-randomization software will be used. One of the study dietitians will log into the webpage and enter the initials of the patient, whereby the patient will get assigned to a treatment. No stratification will be made before randomization.

### Eligibility Criteria

Patients eligible for enrollment must fulfill all the inclusion criteria and none of the exclusion criteria shown in Textbox 1**.**

Inclusion and exclusion criteria for participation in the Carbohydrates in Irritable Bowel Syndrome (CARIBS) trial.
**Inclusion and exclusion criteria for participation in the trial**

**Inclusion criteria**
Irritable bowel syndrome, according to Rome IVAged ≥18 yearsIrritable bowel syndrome Severity Scoring System score ≥175Gothenburg region resident
**Exclusion criteria**
Any other serious disease or illnessOther gastrointestinal diseases, including celiac diseaseOther diseases that may affect gastrointestinal function, including bariatric surgeryAllergy or food hypersensitivity (other than lactose intolerance)Any (major) dietary restrictionsPregnant or breastfeedingBMI ≤18 kg/m^2^ or ≥35 kg/m^2^Unable to communicate in SwedishPreviously been treated with any of the intervention arms, including having tested all the pharmacological treatment options of relevance for the symptom profile of the patient

### Recruitment

Patients will be recruited by referral to a dietitian or physician at a specialized GI unit at the Sahlgrenska Hospital, Gothenburg, Sweden, or through advertising. Patients referred to the unit from, for example, primary care, will be sent an invitation letter with a proposal to participate in the study, and upon approval, they will be scheduled for a screening visit at the clinic. Patients will also be recruited through advertisements in local newspapers or social media platforms.

### Sample Size

The power calculation is based on the primary outcome, where the expected response rate is set to 40% (LCD), 65% (LFTD), and 40% (OMT) in the treatment arms. With 80% power to detect differences between groups, and α=.05, 83 patients will be needed in each group. To account for a 15% dropout rate, we will assign 100 patients to each treatment arm.

### Participant Timeline

The study comprises a 10-day screening period, followed by a 4-week intervention and a 6-month follow-up period. An overview of the enrollment, allocation, and intervention process is shown in Figure 1.

In short, at the first visit, after receiving verbal and written information about the study, all patients will provide their written informed consent. The diagnosis of IBS will be confirmed by a physician, who will perform a physical examination and ensure that the patients fulfill the Rome IV criteria for IBS [1]. Thereafter, a 10-day screening period will begin, where a daily stool diary based on the Bristol stool form (BSF) scale [17] will be completed, and a 4-day food record will be kept. On their return visit, the patients will complete the IBS-SSS to assess the severity of their IBS symptoms during the 10-day screening period. Patients who score ≥175 on the IBS-SSS (ie, moderate to severe IBS symptoms) will be eligible to be randomized into one of the treatment arms. Patients with an IBS-SSS score <175 will be excluded from further participation and will be offered a regular visit to a dietitian or physician at the clinic.

**Figure 1 figure1:**
[figure not shown]
A schematic overview of screening, allocation, intervention, and follow-up. Blood samples include (a) tissue transglutaminase, immunoglobulin A, hemoglobin, white blood cells, platelets, sodium, potassium, creatinine, calcium, c-reactive protein, thyroid-stimulating hormone, free thyroxine, aspartate aminotransferase, alanine aminotransferase, albumin, and (b) plasma glucose, glycated hemoglobin, cholesterol, high-density lipoprotein, low-density lipoprotein, triglycerides. BSF: Bristol stool form; CSI: Central Sensitization Inventory; FODMAP: fermentable oligo-, di-, monosaccharides and polyols; GSRS-IBS: gastrointestinal symptom rating scale-IBS; HAD: Hospital Anxiety and Depression Scale; HSP: Highly Sensitive Person scale; IBS: irritable bowel syndrome; IBS-QoL: IBS quality of life; IBS-SSS: IBS severity scoring system; MFI-20: Multidimensional Fatigue Inventory-20; VSI: Visceral Sensitivity Index; WPAI-IBS: work productivity and activity impairment questionnaire.

Questionnaires assessing GI symptoms, extraintestinal and psychological symptoms, fatigue, QoL, and work productivity will be completed after allocation and before starting the intervention, at the end of the intervention period, and during follow-up. A 4-day food record will be repeated twice during the follow-up period. During the intervention period, participants will be instructed to complete a daily stool diary (BSF) and note any deviation from their allocated diet intervention. The patients will also complete questionnaires on a weekly basis to assess the severity of their GI symptoms (IBS-SSS and the GI Symptom Rating Scale-IBS [GSRS-IBS]).

### Interventions

#### Overview

Upon fulfilling all the inclusion criteria and none of the exclusion criteria, the patients will be randomized and receive LCD, LFTD, or OMT. The dietary treatment will be administered by a dietitian and the pharmacological treatment by a physician. All patients will be informed that both diets and medical treatments aim to relieve their symptoms and that none of the treatments are believed to cure IBS.

##### Overview of Dietary Treatments

Participants assigned to a dietary intervention will receive oral and written information about their diet. No detailed information about the compositions or names of the diets will be given. All foods included in the intervention will be delivered to the patient once a week using a conventional grocery supplier with a home delivery service. A booklet with practical considerations, detailed meal plans, recipes, and lists with foods that are allowed and not allowed during the intervention will be provided. The recipes are based on a standardized energy level, regardless of the energy requirement; thus, patients will be instructed to either eat less or add extra foods if needed (according to the lists provided) to maintain weight stability. If patients need to deviate from their detailed meal plan, all deviations from their diet will have to be reported in a daily symptom diary. After 2 weeks of intervention, patients will be contacted by email to check for compliance and record any adverse events.

##### LCD Intervention

The LCD comprises mainly starch-free vegetables, fish, poultry, beef, dairy products, eggs, nuts, seeds, berries, and fruits that are low in carbohydrates (ie, kiwi, pomegranate, and grapefruit). The diet comprises approximately 10% of total energy (E%) from carbohydrates, 25 E% protein, and 65 E% fat. Detailed information about the nutritional compositions can be seen in Table 1. Patients allocated to this diet will be informed to avoid starchy and sugary foods, such as pasta, rice, potatoes, bread, fruits, and confectionaries. Owing to the reduction in total carbohydrates—and thus the sources of dietary fibers—nuts and seeds are included, providing approximately 25 grams of dietary fiber/day. For participants who normally consume a lactose-free diet, the LCD can be offered without lactose as well.

**Table 1 table1:** Mean daily energy and nutrient intake in diet A and B.

Energy and nutrients	LCD^a^	LFTD^b^
Energy (kcal), mean (SD)	2353 (158)	2380 (217)
Carbohydrate (g), mean (SD)	48 (10.8)	278 (27.6)
Fat (g), mean (SD)	178 (19.6)	89 (16.4)
Protein (g), mean (SD)	133 (17.1)	99 (16.7)
Dietary fiber (g), mean (SD)	25.4 (5.7)	30.2 (5.4)
Vitamin C (mg), mean (SD)	169 (83.8)	210 (112.1)
Iron (mg), mean (SD)	13.6 (2.8)	12.2 (2.8)
Total FODMAP^c^ (g), mean (SD)	16.6 (7.0)	3.4 (0.9)
Lactose (g), mean (SD)	6.3 (3.8)	0.2 (0.2)
Fructose in excess of glucose (g), mean (SD)	2.0 (2.3)	0.7 (0.9)
Fructan (g), mean (SD)	3.3 (1.1)	1.7 (0.3)
Galacto-oligosaccharides (g), mean (SD)	1.1 (2.4)	0.3 (0.1)
Polyols (g), mean (SD)	3.7 (3.0)	0.4 (0.3)
Carbohydrate (E%^d^)	10	50
Fat (E%)	67	33
Protein (E%)	23	17
Saturated fat (E%)	25	11
Monounsaturated fat (E%)	25	11
Polyunsaturated fat (E%)	9	9
Total weight of food (g/day), mean (SD)	1368 (148)	1850 (206)
Proportion of animal foods^e^, (%)	50	30

^a^LCD: low-carbohydrate diet.

^b^LFTD: low FODMAP and traditional dietary advice.

^c^FODMAP: fermentable oligosaccharide, disaccharide, monosaccharide, and polyol.

^d^Percentage of calories from total energy intake.

^e^Meat, poultry, fish, shellfish, egg, and dairy.

##### LFTD Intervention

Patients will be advised to eat small meals on a regular basis, with 3 main meals and 3 snacks each day. All meals should be eaten slowly, and the food should be chewed properly; vegetables and fruits will be recommended to be peeled or boiled; food triggers such as coffee, alcohol, fizzy drinks, sweeteners, and fatty and spicy foods will be limited. Intake of dietary fibers will be approximately 30 g/day and mainly comprise soluble fibers from oats, gluten-free bread, chia seeds, vegetables, and fruits. This diet will also be low in FODMAPs and, therefore, will not contain any lactose, onions, legumes, wheat-based products, and high-FODMAP fruits and vegetables. Detailed information about the nutritional compositions can be seen in Table 1.

##### OMT Intervention

Patients assigned to receive OMT will have their predominant GI symptoms and their history of medications assessed by a physician. After that, a choice of evidence-based medical treatment based on the patient’s predominant symptoms will be made, using the list shown in Textbox 2, with a preference for first-line options if they had not been tried before (eg, bulking agent or osmotic laxative for constipation and loperamide for diarrhea). The medications will be tested for 4 weeks, and only 1 medication will be allocated per patient. After 2 weeks, the patient will be contacted by the physician by telephone to check for compliance to treatment and adjust the dosage if necessary. If the medication is terminated because of, for example, side effects by the patient before 4 weeks, no alternative medication will be given during the intervention period.

Pharmacological treatment options based on predominant symptoms with the used starting dose.
**Treatment options based on symptoms with the used starting dose**

**Constipation**
Bulking agent (Sterculia) 4 g once a dayOsmotic laxative (Macrogol) 13.125 g once a dayLinaclotide 290 µg once a day
**Diarrhea**
Loperamide 2 mg twice a dayCholestyramine 4 g once a dayOndansetron 4 mg once a day
**Abdominal pain**
Chronic/frequent pain: Amitriptyline 25 mg before bedEpisodic pain: Hyocyamin 0.2 mg as neededPain with diarrhea: Amitriptyline 25 mg before bedPain with constipation: Linaclotide 290 µg once a day

#### Follow-up

After their third visit, participants in the OMT arm will end their formal participation in the trial and will be offered a regular visit to a dietitian if wanted. However, they will be contacted by mail after ≥6 months with questions regarding the severity of their GI symptoms and the current treatments being used. They will be financially compensated for the cost of the medication during the intervention. Patients in the dietary intervention arms will be informed that during the next 6 months, they may or may not continue with their allocated diet, and structured follow-up visits with repeated 4-day food records will be scheduled at 3 and 6 months after the end of the intervention.

#### Systematic Follow-up on Low FODMAP and Traditional Dietary Advice Treatment

Patients in the LFTD arm will be given a structured rechallenge schedule to be able to test whether individual FODMAPs are tolerated. The schedule comprises a comprehensive list of food items within each FODMAP category and selected foods that are suitable for rechallenge tests. The preference of the participant decides which category to test first, and only 1 FODMAP category will be rechallenged at a time. The amount of the selected food will be increased for 3 days to evaluate tolerance and tolerance levels. After a washout period of 4 days, when all FODMAPs will again be limited, the next FODMAP category can then be rechallenged. When individual tolerance to FODMAPs has been evaluated, the patients will be encouraged to reintroduce FODMAPs in their diet in amounts that can be well-tolerated.

#### Blinding

Patients allocated to the dietary treatment options will be given detailed information about the foods included in the diet but will not be given any specified name of the diet (eg, low FODMAP or low-carbohydrate, high-fat diet). Medical treatment will be open label. Data entry and analyses will be performed by persons blinded to the group assignment.

#### Research Ethics Approval

The project has received ethical approval from the ethics examination authority of the regional ethics committee in Gothenburg (Dnr 278-16).

#### Consent

Written informed consent will be obtained from all study participants before they enter the study. All patients will be informed that consent may be withdrawn at any moment if they so wish, without any further notice.

### Data Collection Methods

#### Food Records

Participants will record all foods and drinks consumed during 4 consecutive days before the allocation visit and twice during the follow-up period, which means that random weekdays and weekends will be combined. Verbal and written instructions on how to complete the food record will be given, and patients will be encouraged to maintain their regular diet during the recording days. All records will be kept in a booklet that will be provided, and detailed information about the consumed foods and drinks will be required. Quantities will be estimated using household utensils or standard measures, and food labels and cooking methods will be noted. Trained dietitians will enter all diet records into the nutrient calculation software.

#### Energy and Nutrient Calculations

Energy and nutrient intakes will be calculated using the software Dietist XP 3.1 (kostdata), which is linked to a Swedish food composition table provided by the National Food Agency, including a FODMAP database add-on [18]. The FODMAP database is aggregated from published sources of analyzed FODMAP content and includes fructose, fructan, lactose, galacto-oligosaccharide, and polyol content (gram/100 g). As only fructose in excess of glucose counts as a FODMAP, excess fructose will be calculated by subtracting the intake of fructose (gram) from glucose (gram) for each separate meal. If the glucose content is higher than the fructose content, a value of 0 will be denoted for excess fructose. The intakes of nutrients will be first summarized for each meal, and thereafter summarized into intakes per day, and finally presented as the mean intake for all 4 days. Cutoffs for reliable habitual energy intake will be set for energy levels ≤800 kcal/day or ≥4500 kcal/day.

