#### Secondary Outcome

The secondary outcomes are as follows:

A more conservative cutoff limit in IBS-SSS reduction will be tested, both with a score reduction of ≥100 and ≥50% of the initial IBS-SSS score. Proportions between treatment arms will be compared using chi-square tests.The absolute and percent change in IBS-SSS and GSRS-IBS from randomization visit to the end of intervention period will be analyzed using paired-sample *t* tests within groups and analysis of variance (ANOVA) between groups.Compliance to treatment in relation to treatment outcome will be analyzed using linear regression, with the measure of compliance as the independent variable and IBS-SSS as the dependent variable.Predictors of response to treatment (demographics questionnaire data, microbiota, metabolites, and immunology) will be analyzed using logistic regression, with *responders* and *nonresponders* as the binary outcome variable.Determinants of GI symptoms will be assessed using linear regression, with GSRS-IBS and IBS-SSS as dependent variables.Maintained adherence to dietary intervention will be assessed using food diaries at 3- and 6-month follow-ups, and differences in nutrient intake will be compared between the 2 diets using unpaired-sample *t* tests. Predictors for long-term adherence to diet will be analyzed using logistic regression, with *adherence* and *nonadherence* as binary outcome variables.Changes in extraintestinal symptoms, QoL, work productivity, and psychological factors in relation to treatment will be analyzed using ANOVA for continuous variables and chi-square tests for categorical variables.

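### The excess-fructose formula is written backwards (glucose minus fructose), against its own definition, its zero rule and Table 1; probably a wording slip, but the sentence needs correcting and the calculation checking

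*Protocol article*

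**What the plan says.** All of the relevant text in the protocol article's Energy and Nutrient Calculations section sits within a few sentences.

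- **Definition.** The sentence opens "As only fructose in excess of glucose counts as a FODMAP".
- **Formula.** It continues: "excess fructose will be calculated by subtracting the intake of fructose (gram) from glucose (gram) for each separate meal".
- **Zero rule.** The next sentence reads: "If the glucose content is higher than the fructose content, a value of 0 will be denoted for excess fructose".
- **Aggregation.** "The intakes of nutrients will be first summarized for each meal, and thereafter summarized into intakes per day", and the daily values are then averaged over the four recorded days.

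Table 1 (LCD Intervention section) has a row for fructose in excess of glucose, with means of 2.0 g for LCD and 0.7 g for LFTD. Excess fructose is one of five components listed beside total FODMAP.

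Food records are kept before allocation and twice in follow-up (Food Records), at 3 and 6 months (Follow-up). Under Secondary Outcome, "differences in nutrient intake will be compared between the 2 diets using unpaired-sample" t tests.

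**The concern.** To subtract fructose from glucose is to compute glucose − fructose. The definition needs fructose − glucose. The zero rule makes sense only for the second direction: under the first, it removes exactly the meals that would give a positive value and leaves those that give a negative one. The formula therefore conflicts with the text on both sides of it.

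The quantity at stake is calculated FODMAP intake from the food records at screening, 3 months and 6 months. Those records feed the secondary comparison of nutrient intake between the two diets. They also bear on the specific aim about reintroducing FODMAPs. If the literal rule were coded and its negative values kept, a patient who ate more fructose in excess of glucose would be recorded as having a lower total FODMAP intake.

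**Working it through.** **Inputs.** The definition, formula and zero rule come from Energy and Nutrient Calculations. The component means and totals come from Table 1 (g/day).

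| | Lactose | Excess fructose | Fructan | Galacto-oligosaccharides | Polyols | Stated total |
|---|---|---|---|---|---|---|
| LCD | 6.3 | 2.0 | 3.3 | 1.1 | 3.7 | 16.6 |
| LFTD | 0.2 | 0.7 | 1.7 | 0.3 | 0.4 | 3.4 |

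**Step 1: reproduce the stated totals with excess fructose positive.**

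- LCD: 6.3 + 2.0 + 3.3 + 1.1 + 3.7 = 16.4, against 16.6 (gap 0.2).
- LFTD: 0.2 + 0.7 + 1.7 + 0.3 + 0.4 = 3.3, against 3.4 (gap 0.1).

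Six figures are each rounded to 0.1, so rounding alone can produce a gap of up to 6 × 0.05 = 0.3. Both gaps fit. With excess fructose left out, the sums are 14.4 and 2.6 (gaps 2.2 and 0.8). With it entered as negative, they are 12.4 and 1.9 (gaps 4.2 and 1.5). Neither alternative fits.

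**Step 2: apply the written rule to a single meal.** Let f be fructose and g be glucose. As written, the value is 0 if g > f, and g − f otherwise.

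| f (g) | g (g) | As written | max(0, f − g) |
|---|---|---|---|
| 5 | 3 | −2 | 2 |
| 3 | 5 | 0 | 0 |
| 4 | 4 | 0 | 0 |

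In every case the written rule equals −max(0, f − g). It is the intended quantity with its sign flipped, so no meal can give a positive value. On 100,000 simulated pairs the largest value was 0.

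**Step 3: illustrate the size on the stated Table 1 totals.** Let T be the stated total and E the stated excess fructose. If negative values are carried into the sum, the total becomes T − 2E. If negative values are also set to 0, it becomes T − E.

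| | T | E | Negatives set to 0: T − E | Negatives carried: T − 2E |
|---|---|---|---|---|
| LCD | 16.6 | 2.0 | 14.6 (−12%) | 12.6 (−24%) |
| LFTD | 3.4 | 0.7 | 2.7 (−21%) | 2.0 (−41%) |

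The difference between the diets is 16.6 − 3.4 = 13.2 g. It would become 14.6 − 2.7 = 11.9 g (−10%) or 12.6 − 2.0 = 10.6 g (−20%). The distortion would not cancel in a between-diet comparison.

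**The case against.** The strongest reply is that the text corrects itself. The definition comes before the slip and a zero rule that fits only fructose − glucose comes after it. An excess that is never positive would be noticed as soon as anyone looked at the output. Table 1 is positive and adds up with the correct sign, so the only evidence on actual practice favours a transposed phrase over a faulty calculation. This stands, and it limits the weight of the point.

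The reach is also limited. The primary outcome is an IBS-SSS responder rate and uses no food records. Compliance during the 28 days is scored from deviations against food lists, not from calculated FODMAP grams. The secondary outcome speaks of nutrient intake without naming total FODMAP. These points stand too.

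A reader might go further and infer that FODMAP intakes in this trial are understated, or that records have already been processed with the wrong sign. The documents do not support this: no understated figure appears in them, and nothing suggests that such records exist. It would be equally wrong to quote only the 24% and 41%, which need negative grams of a nutrient to be carried into a total.

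The reply does not remove the need for a check. Table 1 describes the composition of the planned diets, not how participants' records are processed. Its positive values rule out the two written sentences applied together. Taken alone, they would not rule out a calculation that kept glucose − fructose and skipped the zero rule. The article also does not leave this rule to another document: it states the rule, and states it backwards.

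**Conclusion.** The formula is wrong as written. It contradicts its own definition, its zero rule and the positive values in Table 1, and this follows from the text with no outside assumption. It is most likely a wording slip, and no reported figure is shown to be wrong.

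If coded literally, total FODMAP on the Table 1 diets would fall by 12% to 24% (LCD) and 21% to 41% (LFTD). The range depends on whether negative values are set to 0 or carried. It assumes that the Table 1 means were formed with the correct sign, and it applies to the planned diets only. The effect in participants' own records depends on what they ate and cannot be computed from the article.

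At stake are the food-record FODMAP intakes at screening, 3 months and 6 months, and the secondary nutrient-intake comparison. The primary IBS-SSS analysis and the sample size are unaffected. This is a minor correction worth making, because a stated calculation rule should be right.

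**What to change.** Replace the formula and its zero rule with one statement: *excess fructose per meal = max(0, fructose − glucose), summed per day and averaged over the 4 days.*

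Then confirm that the nutrient calculation applied to participants' food records uses this direction. One meal with more fructose than glucose and one with less, worked by hand and compared with the output, will settle it. Recalculate records only if the check shows that the other sign was used.

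The cost is one sentence and a short check. At the article's data cut (May 2021), 77 of the proposed 200 diet-arm participants had reached visit 5, so most follow-up records were still to come.
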